### Participants

This study focuses on patients of the Saltro Thrombosis Service who voluntary choose to start with self-management. The Thrombosis Service states several inclusion criteria for their patients to start with self-management. The first criterion is a long-term indication for anticoagulants as the training period and investments exceed the regular three to six months of short-term anticoagulant prescription. In 2013, 85% of the patient population of the Thrombosis Service suffered from long-term indication for anticoagulants. Secondly, internet access is mandatory as monitoring of patients by the Saltro Thrombosis Service is provided by the web portal. In the Netherlands 95% of the people have internet access at home. The average age of patients of the Saltro Thrombosis Service is 65 years. In 2013, 61% of Dutch people over 65 used internet daily and over 75% used it during the last three months [18]. Of people aged between 55 and 65, 81% used internet on a daily basis [19]. Third, one must have stable INR values: during a period of at least five days at least two INR values must be within therapeutic range. Patients who meet the criteria for self-management will be approached for participation in the study. Because self-management is already a regular care process of the Saltro Thrombosis Service, the group training is also available for people who are not willing to enter the study. The e-learning is dedicated for participants of the study as this is a new implementation method.

### Recruitment of patients

Patients of the Saltro Thrombosis Service who receive regular care will be recruited. In 2013, 8950 patients received usual care from the Saltro Thrombosis Service, of which 85% with long-term indications. A random selection of 1632 patients was approached for participation in the study using three methods:First a randomly selected group of 475 patients was informed by letter. Of these, 233 patient responded and 59 were willing to participate in the study.Second we approached patients through personal invitation by nurses of the Saltro Thrombosis Service who collect blood by venipuncture. All nurses were trained by the research team to inform patients well about the study and research goals. During five months, nurses actively informed 692 patients about self-management. Of those, 139 patients were interested to participate in the study. In addition, 234 were interested in self-management too, but not in participation in the study.Third we recruited patients by telephone. Two trained research assistants called patients at home to inform them about the possibilities of self-management and about the study. By telephone 465 patients were approached, of which 111 were willing to participate in the study. In addition, 52 patients signed up for self-management but were not willing to participate in the study.

Participants were only included in the study after written informed consent was received. Because not all patients signed an informed consent, 247 participants were finally included. Of these, 110 continued to receive regular care and 137 patients were randomly divided in group 1 and 2 using a computer program. In group 1 (e-learning) 63 patients were included and in group 2 (group training) 74 patients were included. In Fig. 2 recruitment is summarized.

**Fig. 2 Fig2:**
[figure not shown]
Schematic summary of recruitment; A schematic summary of the number of eligible patients, how many of them were approached, with what method they were approached, how many responded, how many are participating, and in which group

Patients who are willing to participate will receive rewards: a € 25,- gift card after completing the first set of questionnaires and a € 50,- gift card after completing the last set of questionnaires after 18 months.

### Responder analysis

The total population of the Saltro Thrombosis Service on January 1^st^, 2014 was 10.209 patients of which 8.939 patients received regular care (eligible patients) and 1.271 self-management (894 self-monitoring and 377 self-dosage). 53% were men and 47% women. The mean age was 73 years (SD 14). In the study population 247 patients were included of which 72.9% were men and 27.1% women. The median age was 66.9 (IQR 59.5–72.7) years in the total group; 65 years in group 1 and 65.8 years in group 2, and 69.6 years in group 3.

Analysis showed a significant difference in median age between the groups. Younger men participated in the PORTALS trial compared to patients who declined participation. The average INR of the participants did not significantly differ from the eligible population at the start of the study. In Fig. 3 the characteristics of the patients are summarized.

**Fig. 3 Fig3:**
[figure not shown]
Characteristics of eligible patients versus included patients; The average age, percentage of males, and average INR of eligible patients versus included patients is shown

Among patients who were recruited by letter we asked non-participants to inform us about their reasons. 35 patients filled in the non-responders form 12 patients did not want to start self-management because they had no computer or internet access, 7 patients were satisfied with regular care and wanted to continue it, 6 patients felt they were too old, 10 patients had other reasons such as painful fingers (1), physical inabilities (2), training is too much effort (2), insecurity (2) or unknown reasons (3).

### Allocation procedure

Participants were randomly selected for e-learning (group 1) or group course (group 2) during the registration procedure for the training by a computerized program. Participation in group 3 was not randomized but free choice for patients.

In Fig. 2 the total amount of included patients is summarized.

### Intervention

This study investigates the effect of different implementation strategies on adequate training for self-management skills in patients with AT expressed in TTR, as well as potential determinants of the effect. We compare group training versus e-learning. Patients who follow e-learning have to pass at least three modules. The first module contains general education about anticoagulation including test questions. Patients can only successfully pass this first module after all questions are answered correctly. They then receive a written confirmation. With this confirmation patients can pick up a self-testing device at one of the Saltro Thrombosis Service locations. Furthermore, patients get access to the second module that teaches them to use the self-testing device. After one or two weeks patients have an appointment with a nurse of the Thrombosis Service Centre to show their self-testing skills. If the skills are sufficient, the nurse explains the patients how to use the online web portal. The following three months a training period is applicable, during which patients measure their INR weekly and inform the Thrombosis Service using the web portal. After three months, patients have another control appointment to check their self-testing skills technique and adequate use of the web portal. If patients are able to provide reliable INR values by self-measurement and if they adequately use the web portal to inform the Thrombosis Service about testing results and relevant medical information, the self-monitoring training is ended. From that moment on, patients have control appointments with the nurse every six months. In addition, patients are offered to continue with training in self-adjustment of medication dosage. This training is only available in a group course.

The group training consists of two meetings. During the first meeting patients are trained to use the device to measure their own INR and they are trained to use the web portal. Patients practice at home for three weeks. At the second meeting the capillary technique of patients is checked by nurses of the Thrombosis Service. In addition, patients receive general education about anticoagulation. The following three months a training period is applicable during which patients measure their INR weekly and inform the Thrombosis Service using the web portal. After three months patients have a control appointment with the nurse to check their capillary technique and to discuss the training period. If patients are able to provide reliable INR values by self-measurement and if they adequately use the web portal to inform the Thrombosis Service about testing results and relevant medical information, the self-management training is ended. From that moment on, patients have control appointments with the nurse every six months. In addition, patients are offered to continue with training in self-adjustment of medication dosage. This training is only available in a group course.

The regular care group receives traditional thrombosis care, which means a basic instruction by nurses of the Saltro Thrombosis Service in their own home. Patients are explained what locations they can go to for venous puncture. Based on analyses of the blood samples (INR values) professional thrombosis doctors give written instructions about medication dosage and lifestyle to the VTE patients. This also includes indication for follow-up puncture.

All training schedules are summarized in Fig. 4.

**Fig. 4 Fig4:**
[figure not shown]
Time course for group 1, 2 and 3; The three groups and the time courses of their trainings, blood testing procedures, and instructions

### Data collection

The data collection consists of questionnaires to measure the determinants and secondary outcomes, that patients of group 1 and 2 receive by e-mail. Patients in research group 3 (who do not work with the web portal) receive the same questionnaires either by e-mail or post. In case of non-response we will send two reminders by mail or email and will approach the patients once by telephone. In Fig. 5 planning of measurements is summarized. There are four measurements in this study during a period of 18 months. INR values and thromboembolic events are monitored and registered daily by professionals of the Saltro Thrombosis Service. In addition health care use, the number of self-tests and use of the portal are continuously registered in the web portal. Data collection is summarized in Fig. 5.

**Fig. 5 Fig5:**
[figure not shown]
Measurements over time; A schematic overview of the different types of measurements on T1 = 0, T2 = 6, T3 = 12, and T4 = 18 months

### Outcome parameters

At first we compare clinical outcomes (TTR) and complications between three groups; second we compare TTR, complications and self-management skills of two different implementation methods in group 1 and 2. Second, the relationship between self-management skills, clinical outcomes, and individual characteristics will be investigated.

#### Primary outcome

Health status is the primary outcome, expressed by TTR and severe complications (bleedings and thromboembolic events). TTR is computed as INR values within therapeutic range based on individual targets, calculated with the Rosendaal method [20]. INR values will be measured using a whole blood PT/INR monitor (CoaguChek, Boehringer Mannheim, Germany). Bleedings and thromboembolic events will be registered in patient files by professionals of the Saltro Thrombosis Service during the total study period of 18 months. Events can be reported by general practitioners and hospital professionals by e-mail or telephone, or by patients themselves using the online portal, e-mail, or telephone.

In this study, adequate self-management skills are defined as a) the ability to correctly measure one’s own INR; b) the ability to use the online web portal to report all measured INR values; c) the ability to use the online web portal to report all relevant medical conditions and d) the ability to correctly calculate dosage schedules. The latter being only applicable if patients voluntary choose to self-adjust their own medication intake. Correct self-testing of INR will be judged by thrombosis nurses during yearly control visits. We registered the usage of the self-management platform, including sharing of information and calculation of medication dosage; the amount of login sessions will be used as a measure for self-management skills. The usage counts will be analyzed.

#### Determinants

We expect that the relationship between the level of self-management skills and clinical outcomes is influenced by socio-demographic, (psycho) social characteristics, and self-efficacy.

*Self*-*efficacy* is measured using the Generalized Self-Efficacy Scale (GSES), which will be displayed at baseline. This 10-item questionnaire was designed in 1981 by Jerusalem en Schwarzer [21]. The items are scored by a four-point scale on which a higher score reflects higher self-efficacy. Research in 28 countries showed that Cronbach’s alpha varies between .76 and .90, of which mostly above .80 [22].

*Socio*-*demographic characteristics* will be assessed by a purpose-designed questionnaire (online). As use of the web portal is part of the self-management program and as decreased access to internet and low general health outcomes have been associated with lower socioeconomic status, minority racial/ethnic groups, older age, and poorer health we will also include the following characteristics in our questionnaires: age, socioeconomic status, marital status, and general use of online and digital products and services.

#### Secondary outcomes

*Quality of life* (QoL) is assessed using the EuroQol-5D (EQ-5D). This questionnaire contains 5 items with a 3-point Likert scale. A higher score reflects a higher quality of life. The EQ-5D comprises 5 levels: mobility, self-care, daily activity, pain/discomfort, and anxiety/depression. Research showed that the EQ-5D is a reliable and valid questionnaire [23]. The EQ-5D can be used to compute QALY’s, which are necessary to evaluate cost-effectiveness.

*Direct costs* of both intervention methods will be included in this study. Intervention costs include development costs of e-learning and costs of group courses. Development costs are provided retrospectively by the owner of the portal. Implementation costs are administered by the research group, and mainly consist of personnel costs and practice materials.

*Health care use of the Saltro Thrombosis Service is constantly registered* in this study the health care use of the Saltro Thrombosis Service is constantly registered.

### Data analyses

Baseline characteristics between the 3 groups will be explored using Chi-square tests and Kruskal-Wallis tests.To investigate the effect of different implementation methods of training versus the parallel cohort group, TTR and complications between groups will be analyzed using multilevel linear regression modelling (mixed models). First, outcomes will be compared between the three groups. A second analysis will be used to compare the difference in effect between e-learning and group training (group 1 vs group 2) on TTR, complications and usage using mixed models. Analyses will be adjusted for age and gender.To examine the impact of GSES and education on the effect of different implementation methods, those variables will be included in the mixed models.

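### Severe complications, part of the primary outcome, are assigned a linear mixed model, which does not suit a small number of events over varying follow-up

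*Protocol article*

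**What the plan says.** The Primary outcome section defines the endpoint in two parts: "Health status is the primary outcome, expressed by TTR and severe complications (bleedings and thromboembolic events"). On the second part it adds that "Bleedings and thromboembolic events will be registered in patient files by professionals of the Saltro Thrombosis Service during the total study period of 18 months".

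The Data analyses section names one model family for both parts: "TTR and complications between groups will be analyzed using multilevel linear regression modelling (mixed models"). This is used first for the three groups. A second analysis compares e-learning with group training "on TTR, complications and usage using mixed models". Both are adjusted for age and gender. No logistic, Poisson or time-to-event model is named for complications, and follow-up time is not mentioned.

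On sizes, the Recruitment section reports that "In group 1 (e-learning) 63 patients were included and in group 2 (group training) 74 patients were included", and that 110 patients stayed in usual care. The Power calculation section allows for 15% dropout. The article gives no complication rate.

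**The concern.** TTR is a continuous percentage, and a linear mixed model is a reasonable choice for it. Complications are a different kind of variable: most patients will have none, and a few will have one or more. Three features of a linear model then cause trouble.

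- **Follow-up time.** Patients who drop out are at risk for less than 18 months. The model as named has no term for this.
- **Variance.** For event data the variance moves with the rate. A linear model uses one pooled residual variance, so the standard error of a contrast between two groups depends partly on how many events the third group had.
- **Range.** Nothing keeps fitted risks or their limits at or above zero.

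At stake are the intervals and p-values for one of the two components of the primary outcome. The article makes this choice explicitly, so it is not a detail left open for an analysis plan.

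**Working it through.** **Inputs from the article.** Group sizes 63, 74 and 110; 18 months of follow-up; TTR SD 10, difference 5, power 80%, α = 0.05.

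**Assumed.** 0.01 to 0.10 complications per patient over the study, because no rate is given.

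**The article's own figure.** n = 2 × (1.96 + 0.842)² × 10² / 5² = 62.8, so 63 per group, as stated. This is for TTR. No figure is stated for complications.

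**Two groups, 63 against 74.** The linear comparison (one total per patient, pooled variance, unadjusted) was simulated 20,000 times per setting with Poisson events. The last two columns give 95% interval coverage when group 1's rate is doubled or halved.

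| Events per patient | Expected events (groups 1, 2) | Type I error | Coverage, doubled | Coverage, halved |
|---|---|---|---|---|
| 0.01 | 0.6, 0.7 | 0.3% | 85% | 65% |
| 0.02 | 1.3, 1.5 | 1.2% | 91% | 85% |
| 0.03 | 1.9, 2.2 | 2.8% | 94% | 89% |
| 0.05 | 3.2, 3.7 | 4.1% | 94% | 95% |
| 0.10 | 6.3, 7.4 | 5.0% | 94% | 96% |

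Exact enumeration with 0/1 outcomes gives nearly the same type I errors: 0.2%, 1.4%, 2.7%, 4.2% and 4.7%. At 0.01 to 0.03, the usual interval for the group 2 mean extends below zero in 52 to 72% of data sets.

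**One data set, 0/63 against 3/74.**
- Residual variance: 3 × (1 − 3/74) / 135 = 0.0213.
- Standard error of the difference: √[0.0213 × (1/63 + 1/74)] = 0.0250.
- t = 0.0405 / 0.0250 = 1.62, so p = 0.108. Fisher's test gives 0.249.
- Interval for the group 1 risk: 0 ± 1.978 × √(0.0213/63), which is −3.6% to +3.6%. The exact upper limit is 1 − 0.025^(1/63) = 5.7%.

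**Three groups, 0/63 against 6/110, with g events in group 2.** Residual variance = [g(1 − g/74) + 6(1 − 6/110)] / 244, and the difference is 6/110 = 0.0545.

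| g | Residual variance | Standard error | t | p |
|---|---|---|---|---|
| 0 | 0.0232 | 0.0241 | 2.26 | 0.024 |
| 1 | 0.0273 | 0.0261 | 2.09 | 0.038 |
| 2 | 0.0312 | 0.0279 | 1.95 | 0.052 |
| 3 | 0.0350 | 0.0296 | 1.84 | 0.066 |

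The two groups alone give a linear p of 0.060, and Fisher's test gives 0.087. The data being compared are the same in every row; only the third group changes.

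**Unequal rates.** Suppose usual care has rate r and groups 1 and 2 have r/3. The pooled variance is (62 × r/3 + 73 × r/3 + 109 × r) / 244 = 0.631r, against a true 0.333r in groups 1 and 2. The standard error used for group 1 against 2 is too large by a factor √(0.631/0.333) = 1.38. The type I error is then about 2Φ(−1.96 × 1.38) = 0.7%. Simulation gives 0.7 to 0.9% at every rate from 0.01 to 0.10, so more events do not cure this. It applies if that contrast is read from the three-group model.

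**The case against.** The strongest defence has four parts.

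**The error depends on an unstated rate.** This stands. The article does not call complications rare. At 0.02 to 0.05 events per patient-year over 1.5 years, that is 0.03 to 0.075 per patient, the two-group type I error is roughly 3 to 5%.

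**The linear test is not anti-conservative.** A reader might infer from the two examples that linear p-values are generally too small. They are not. The enumerated two-group type I error stays below 5% at every rate checked, for 63 against 74 and for 63 against 110. Fisher's test is itself conservative, so part of each gap belongs to it: mid-p values are 0.17 for 0/63 against 3/74 and 0.056 for 0/63 against 6/110. What remains is poor coverage at low rates and dependence on the third group.

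**TTR carries the trial.** It is the only powered outcome, and the Discussion calls INR and TTR the main outcome. This limits the consequence, but the Primary outcome section still includes complications.

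**Login usage.** A reader might extend the point to login counts, of which the article says "The usage counts will be analyzed". The documents do not support calling that analysis invalid. For usage the text says only mixed models, without linear, and already restricts the comparison to groups 1 and 2. Even a linear comparison holds up: with assumed negative binomial counts of mean 70, type I error is 4.8 to 5.1% and coverage 92.9 to 95.9%. An offset for active portal time is also not advisable, because time to portal access is a consequence of the randomised training.

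**Conclusion.** The point holds for complications only. The article fixes a linear model for an event outcome that is part of the primary outcome, and that choice is unsuitable.

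Its size is conditional on the rate. Over an assumed 0.01 to 0.03 events per patient the two-group comparison is clearly off nominal; from about 0.05 it is close to nominal. In the three-group model the shared variance can move a p-value in either direction and across 0.05, at a fixed result for the two groups compared.

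These figures rest on one total per patient, equal follow-up and no adjustment for age and gender. The adjusted multilevel model may differ in detail. The plan for TTR is not in question.

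**What to change.** Keep the linear mixed model for TTR only. State a separate analysis for severe complications: an event model, for example Poisson regression with log follow-up time as offset, reported as rates per patient-year with rate ratios and intervals. Specify exact or Firth-type estimation if events are few.

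The cost is one paragraph of analysis text and standard software, with no new data. The article describes the trial as ongoing, so the change can be recorded before the complication data are analysed. The downside is small: with few events the intervals will be wide and adjustment for age and gender will be limited.

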**Fig. 1 Fig1:**
[figure not shown]
Subdivision within the Saltro Thrombosis Service into three groups; Groups 1 and 2 perform self-management; group 1 was instructed by e-learning and group 2 by group course. Group 3 receives the usual care, with brief instructions

Due to the nature of this study (implementation research in a real-life care setting) a perfect RCT design is not feasible: patients cannot be forced to start self-management. Patients will however be randomized in group 1 (e-learning) and group 2 (group training). Furthermore, patients unable to dose their medication are free to continue with only self-monitoring. This study will be performed using a parallel cohort design. Although bias may occur, the results of this study remain valuable because in daily practice biases will occur too when it comes to patients voluntary choosing the type of care they are willing to receive. Based on our study design, comparison between e-learning and group training for self-management (group 1 and 2) and non-self-management patients (group 3) is applicable considering specific conditions in the choice of the statistics. Parallel cohort group 3 provides valuable information about patients who are unable or unwilling to use online supported self-management programs.

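### The planned adjustment names no baseline TTR term, which leaves the self-selected group 3 comparison open to confounding and costs precision in the randomised comparison

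*Protocol article*

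**What the plan says.** The Data analyses section plans mixed models for two comparisons: the three groups first, then group 1 (e-learning) against group 2 (group training). It states "Analyses will be adjusted for age and gender". The next sentence adds two variables for a different purpose: "To examine the impact of GSES and education on the effect of different implementation methods, those variables will be included in the mixed models". No baseline TTR or pre-study INR term is named.

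On group 3, the Allocation procedure section says "Participation in group 3 was not randomized but free choice for patients". The text after Fig. 1 accepts that bias may occur, and says that comparing groups 1 and 2 with group 3 "is applicable considering specific conditions in the choice of the statistics".

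Several passages bear on whether earlier INR data exist. The opening of Methods describes participants as current usual-care patients on long-term therapy with frequent INR monitoring. The Participants section makes at least two in-range INR values a condition for self-management. The Power calculation section reports TTR from a pilot of 100 of the service's own patients. The Responder analysis section already uses INR at the start of the study.

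**The concern.** How well a patient's INR was controlled before the study is an obvious predictor of later TTR, which is part of the primary outcome. Patients who choose self-management may differ in prior control from those who decline it, and age and gender need not capture that difference. The groups are known to differ in one respect: median age is 65, 65.8 and 69.6 years in groups 1, 2 and 3. The Discussion section also concedes that factors such as computer ownership and satisfaction with usual care can create bias. If prior control differs too, the three-group comparison would credit or debit self-management with a difference that was there at entry.

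In the randomised comparison the stake is smaller. A prognostic covariate that is probably available goes unused, and the confidence interval is wider than it needs to be.

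**Working it through.** **Inputs from the protocol article.** TTR mean 84%, SD 10; relevant difference 5 points; power 80%; α = 0.05; 63 per group; 15% dropout (Power calculation). Arm sizes 63 and 74; group 3 has 110 and the randomised groups 137 together (Recruitment of patients).

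**Assumed, not in the article.** The correlation r between pre-study and follow-up TTR (0.3, 0.5, 0.7), and a baseline TTR gap of 3 points between group 3 and the others beyond what age and gender explain. SD is taken as 10 at both times, so the regression slope equals r.

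**Step 1: the plan's own figure.** n = 2 × [10 × (1.960 + 0.842) / 5]² = 62.8, so 63 per group. This reproduces with a two-sided test and no covariate, so the sample size does not count on any gain from adjustment.

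**Step 2: randomised comparison.** Residual SD = 10 × √(1 − r²). The standard error is that SD × √(1/n₁ + 1/n₂), and power is Φ(5/SE − 1.96). Without dropout n₁ = 63 and n₂ = 74. With 15% dropout they are 53.55 and 62.9. For r = 0 with dropout, SE = 10 × √(1/53.55 + 1/62.9) = 1.86, and Φ(5/1.86 − 1.96) = 76.7%.

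| r | Residual SD | n per group needed | Power, no dropout | Power, 15% dropout | 95% CI half-width, 15% dropout |
|---|---|---|---|---|---|
| 0 (no baseline term) | 10.00 | 63 | 83.1% | 76.7% | 3.64 |
| 0.3 | 9.54 | 58 | 86.4% | 80.5% | 3.48 |
| 0.5 | 8.66 | 48 | 92.0% | 87.4% | 3.16 |
| 0.7 | 7.14 | 33 | 98.3% | 96.5% | 2.60 |

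Using the t distribution, the dropout column becomes 76.0%, 79.8%, 86.8% and 96.2%.

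**Step 3: comparison with group 3.** Residual bias = r × baseline gap. For a 3-point gap:
- r = 0.3: 0.9 points
- r = 0.5: 1.5 points
- r = 0.7: 2.1 points

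That is 18% to 42% of the 5-point target (0.9/5 and 2.1/5). To show what this does to a test, pool groups 1 and 2 against group 3: SE = 10 × √(1/137 + 1/110) = 1.28. A bias of 1.5 points then raises the two-sided type I error from 5% to about 22%.

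**The case against.** Several counter-arguments have force.

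- *Age and gender are not the only covariates.* True: GSES and education also enter the models. They do so to examine their impact on the training effect, and neither stands in for prior INR control.
- *A full INR history is not documented.* A reader might infer that baseline TTR can be computed for every participant. The article does not say so. The stability criterion guarantees only two values, and the statement "INR values and thromboembolic events are monitored and registered daily by professionals of the Saltro Thrombosis Service" stands in the description of data collection for the study. That earlier values exist is a sound inference; their length is unknown.
- *Average INR was already checked.* The sentence "The average INR of the participants did not significantly differ from the eligible population at the start of the study" sets participants against the eligible population. It is not a comparison of groups 1, 2 and 3, so it neither shows nor rules out a baseline difference between them. The between-group check is in Data analyses, where the variables are not listed.
- *Group 3 may have met the same criteria.* A reader might infer that group 3 contains patients without internet access or stable INR. The Participants section says that those approached met the criteria, and the patients who reported having no computer or internet were non-participants. Against that, the text after Fig. 1 says "Parallel cohort group 3 provides valuable information about patients who are unable or unwilling to use online supported self-management programs", and Data collection allows postal questionnaires for group 3. The sections are not fully consistent, so ineligible patients in group 3 are possible but not established.
- *A mixed model could carry a month-0 TTR as a repeated outcome, and model detail may sit in an analysis plan that is not shown.* The first is possible but stated nowhere. On the second, the article does state an adjustment set, and baseline TTR is not in it.
- *The bias is disclosed.* Disclosure does not remove it from the estimate.

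**Conclusion.** The point holds in a limited form. The stated adjustment for the two main comparisons leaves out the baseline value of TTR, although the data needed are probably at hand.

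It matters most for group 3. There, an assumed 3-point gap would leave 0.9 to 2.1 points of bias for r from 0.3 to 0.7. Nothing in the article shows that such a gap exists, so this is a vulnerability and not a demonstrated bias.

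A reader might infer that the randomised comparison is also biased, or underpowered as enrolled. Neither follows. Randomisation protects it from this confounding, and unadjusted power is 83% with no dropout. It falls to about 76–77% only if the full 15% is lost. Adjustment would then bring it to about 80%, 87% or 96% at r = 0.3, 0.5 or 0.7. The stability criterion may narrow the range of baseline TTR and lower r, so the upper end may be optimistic.

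Adjusting for baseline TTR would reduce self-selection bias in the group 3 comparison but would not remove it.

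**What to change.** 1. Compute Rosendaal TTR over a fixed window before inclusion, state a rule for patients with a short INR history, and prespecify it as a covariate in every TTR model, alongside age and gender.
2. For comparisons with group 3, put GSES, education, socioeconomic status and internet use, which the article plans to collect or analyse, into the main adjusted model.
3. Report the group 3 result as an observational comparison with residual self-selection.
4. Reconcile the Participants section with the text after Fig. 1 on who could enter group 3. If any group 3 patients did not meet the self-management criteria, add a sensitivity analysis restricted to those who did.

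The cost is one extraction from the service's INR records and a few model terms. Some patients may have too short a history for the chosen window, and the restricted analysis, if needed, would use a smaller group 3. The article describes the trial as ongoing, so these changes can be fixed before analysis.
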